**Figure 1 BMJOPEN2015008951F1:**
[figure not shown]
PATHWAY 2 study design and flow chart.

The trial was designed as double-blind, but this incurs considerable extra costs; thus, we decided that the last 100 patients should be studied open-label, in order to determine whether the large extra cost of blinding confers any advantage. For the blinded phase of the trial, the study drugs will be re-encapsulated to provide participants with an identical single capsule throughout, containing either active drug or placebo (microcrystalline cellulose). For the open label cohort, patients will receive drugs according to the randomisation schedule in the original drug manufacturers’ packaging.

During the double-blind phase, none of the investigators, patients or laboratory staff were aware of the assignment. A 24-h telephone unblinding service was provided by the Data Management Centre for instances where principal investigators (PIs) believed that treatment of an adverse event may be compromised by their not knowing the treatment assignment.

Compliance has been assessed by returned tablet counts.

#### Tolerability

Adverse events are recorded in the electronic case record form at each visit. A 2-week drug holiday is permitted at any point if the investigator considers that this may allow participants to remain in the trial without early withdrawal.

#### Run-out phase of the study

To evaluate if amiloride would be a suitable alternative to spironolactone, the run-out phase of the study was used to evaluate the BP-lowering effectiveness of amiloride using an open label design. Patients were eligible for the amiloride open label run-out phase of the study as long as they did not develop potassium levels ≥5.5 mmol/L during the study treatment cycles. If eligible, patients were prescribed open-label amiloride 10 mg once daily for 6 weeks, followed by forced titration to amiloride 20 mg once daily for a further 6 weeks. Patients were evaluated at study sites at 6 and 12 weeks, and BP recorded in accordance with procedures for the main study. In the remaining patients, physicians will choose the exit drug based where possible on pretrial experience of fourth and fifth-line treatment. For patients with uncontrolled BP at the end of the treatment cycles, or the amiloride run-out phase, it was considered unethical to wait for completion of the overall study before their best treatment option could be revealed. Thus, at the end of the main study, the data base will be locked for individual patients and the data centre can reveal the best treatment option for an individual patient at the request of the study site PI. The full schedule of assessment and procedures is shown in the table 1.

**Table 1 BMJOPEN2015008951TB1:** PATHWAY 2 Study schedule and procedures

	Screening	Randomisation	Phase 1		Phase 2		Phase 3		Phase 4	
	Week −4	Week 0	Week 6	Week 12	Week 18	Week 24	Week 30	Week 36	Week 42	Week 48
Informed consent	X									
Medical history	X	X								X
Clinical examination	X									X
Concomitant medications	X	X	X	X	X	X	X	X	X	X
Weight	X	X	X	X	X	X	X	X	X	X
Inclusion/exclusion criteria check	X	X								
Clinic BP and heart rate	X	X	X	X	X	X	X	X	X	X
Home BP and heart rate*		X	X	X	X	X	X	X	X	X
Home BP 6 h after witnessed administration of A+C+D medication†		X								
12 lead ECG	X									X
PEFR	X	X	X	X	X	X	X	X	X	X
Blood tests—electrolytes, urea, creatinine	X	X	X	X	X	X	X	X	X	X
Blood tests—glucose, lipids, uric acid, Ca++	X									X
Blood tests—cholesterol, HDL and triglycerides		X								X
Blood tests –plasma renin/aldosterone‡		X								
Pharmacogenetics§		X								
Blood tests—haematology, albumin, glucose	X			X		X		X		X
Blood—serum ace levels		X								
24 h urinary electrolytes		X								
Urinalysis	X	X		X		X		X		X
HCG testing pregnancy	X	X		X		X		X		
Haemodynamic measures (cardiac output, peripheral resistance, bioimpedance), pulse wave analysis/velocity¶		X		X		X		X		X
Compliance check		X	X	X	X	X	X	X	X	X
Directly observed therapy		X								
AE reporting			X	X	X	X	X	X	X	X
Randomisation		X								
Dispensing	X	X	X	X	X	X	X	X	X	X

*Home BP measurements are recorded twice daily in triplicate in the 4 days leading up to the baseline visit and week 6 and week 12 visits of each treatment cycle.

†To exclude white coat hypertension and confirm adherence.

‡In the event that plasma renin/aldosterone is not taken at baseline, it will be measured at week 12 of each treatment cycle.

§Pharmacogenetics sample to be taken where specific informed consent has been given. Sampling will typically be at baseline (day 0) but may be at any time later in the study.

¶Where equipment is available.

AE, adverse events; BP, blood pressure; HCG, human chorionic gonadotropin; HDL, high-density lipoprotein; PEFR, peak expiratory flow rate.

#### Special considerations

Early randomisation during the 4-week placebo run-in phase, that is, 2 weeks, is allowed for safety reasons for patients developing an excessively elevated BP >180/110 mm Hg or if a fourth background drug has been discontinued at the screening visit or at the discretion of the study site PI. A preplanned break of up to 3 months from the study is permitted, providing patients have completed the previous treatment cycle. A 2-week break from study drugs is permitted to accommodate patients with scheduling problems or for patients with adverse events not definitely attributable to the study drugs. Patients unable to tolerate a drug in a cycle are permitted to move to the next drug in sequence. Extra study visits after dose titration may be arranged at the discretion of the study site PI.

#### Data handling and recording

Study data is recorded via remote data entry into a web-based electronic case report form (eCRF) developed for the study. The data will be collated and held at a single study data management centre, the Robertson Centre for Biostatistics (RCB) and Glasgow Clinical Trials Unit (CTU). The eCRF data is anonymous and will identify study participant by their assigned study numbers only.

#### Ethics approval and study registration

The PATHWAY 2 study has been approved by all relevant ethics committees and all participants will sign informed consent. Consent procedures will be undertaken by trained nursing or clinical staff with delegated authority of the local PI. The PATHWAY 2 study is registered with clinicaltrials.gov; trial identifier; NCT02369081 and EUDract number: 2008-007149-30.

The initial protocol was approved by the Medicines and Healthcare Products Regulatory Agency (MHRA) on 14 January 2009, and is visible at https://www.clinicaltrialsregister.eu/ctr-search/trial/2008-007149-30/GB. It was approved by Cambridge Research Ethics Committee on 12 January 2009. The trial was not registered with Clinicaltrials.gov until 2015 because of the prior registrations with MHRA and UKCRN, and local advice that these sufficed. The current version is 9, dated 23 August 2012. Any further amendments will be approved by Research Ethics and MHRA and also registered with clinicaltrials.gov.’

#### Study participants

The study will randomise 346 patients aged 18–79 years from 14 study sites in the UK. These are the sites represented by the authors, plus Birmingham, Norwich, Manchester, Ixworth and Exeter. Full addresses are at clinicaltrials.gov. All patients will have uncontrolled BP, that is, resistant hypertension despite treatment with maximal/best tolerated doses of a combination of three drugs, that is, A+C+D, according to the recommendations of the current NICE hypertension treatment guidelines.^4^
^5^ Uncontrolled BP is defined as seated clinic systolic BP ≥140 mm Hg for patients without diabetes or ≥135 mm Hg for patients with diabetes, based on a mean of the last 2 of 3 consecutive clinic readings. In addition, the HBPM systolic BP average must be ≥130 mm Hg and within 15 mm Hg of the clinic systolic BP, in the 4 days prior to the baseline visit. Patients who have received three drugs, that is, A+C+D, but are either intolerant to one drug class or tolerate only a lower dose, that is, submaximal recommended dose are eligible. Patients receiving A+C+D and who are also receiving additional drugs for their hypertension may also be included if the investigator (1) considers it is safe and appropriate to stop these additional drug/s at the screening visit and (2) anticipates that the BP criteria for inclusion will still be met after discontinuing the drug/s when rechecked at the baseline visit. Patients can also be included if the HBPM average systolic BP exceeds 130 mm Hg during the run-in period.

Patients are excluded if their clinic systolic BP is >200 mm Hg or diastolic BP >120 mm Hg, but the PI has discretion to over-ride this criterion if home BP measurements are lower. Patients were also excluded if they had secondary or accelerated hypertension; type 1 diabetes (but not type 2 diabetes); an eGFR<45 mL/min or a plasma potassium outside of normal range on two successive measurements during screening, pregnancy, while planning to conceive, or were women of childbearing potential, that is, not using effective contraception; had an anticipated change of medical status during the trial (eg, surgical intervention requiring >2 weeks convalescence); had an absolute contraindication to any of the study drugs (eg, asthma) or a requirement for study drug for reasons other than to treat hypertension (eg, β-blockers for angina or diuretics other than those to treat hypertension, or previous intolerance of the proposed trial therapies, or had sustained atrial fibrillation or a recent (<6 months) cardiovascular event requiring hospitalisation (eg, myocardial infarction or stroke)). Patients were excluded if they were suspected of non-adherence to antihypertensive treatment as determined by a pill count at the end of the 4- week run-in period—those with adherence <70% will be excluded from randomisation, and those with a fall in home systolic BP to <130 mm Hg, 6 h after witnessed administration of their usual A+C+D therapy. A full list of inclusion and exclusion criteria are shown in boxes 1 and 2.

Box 1PATHWAY 2 study inclusion criteriaPatients aged 18–79 yearsPatients will all have hypertension that is not controlled to target: clinic systolic BP ≥5 mm Hg above target (ie, ≥145 mm Hg for non-diabetic hypertensives or ≥135 mm Hg for patients with diabetes), under one of the following conditions:
Treatment for at least 3 months with lisinopril 20 mg (A)+amlodipine 10 mg (C)+bendroflumethiazide 2.5 mg (D) or their equivalentsPatients who have received the three drugs or equivalents specified in (a), and are either intolerant to one category, or tolerate only a lower dose (eg, amlodipine 5 mg or lisinopril 10 mg)Patients receiving the three drugs or equivalents specified in (a), who are receiving additional drugs for their hypertension, may be included if the investigator: (1) feels it is appropriate to stop these additional drugs at the screening visit and (2) anticipates that the BP criteria for inclusion will be met when rechecked at the baseline visitPatients with a home systolic BP average of >130 mm Hg or within 15 mm Hg of clinic BP over the 4 days prior to the baseline visit.

Box 2PATHWAY 2 study exclusion criteriaInability to give informed consent;Participation in a clinical study involving an investigational drug or device within 4 weeks of screening;Secondary or accelerated hypertension;Type 1 diabetes;eGFR<45 mL/min;Plasma potassium outside of normal range on two successive measurements during screening;Pregnancy, planning to conceive or women of childbearing potential, that is, not using effective contraception;Anticipated change of medical status during the trial (eg, planned surgical intervention requiring >2 weeks convalescence);Absolute contra-indication to study drugs (eg, asthma) or previous intolerance of trial therapy;Sustained atrial fibrillation;Recent (<6 months) cardiovascular event requiring hospitalisation (eg, myocardial infarction or stroke);Suspected non-adherence to antihypertensive treatment (see above);Requirement for study drug for reason other than to treat hypertension, (eg, β-blockers for angina or diuretics other than those to treat hypertension);Current therapy for cancer;Concurrent chronic illness, or other reasons likely to preclude 52 week participation in the study;Clinic Systolic BP >200 mm Hg or diastolic BP >120 mm Hg, with PI discretion to override if home BP measurements are lowerAny concomitant condition that, in the opinion of the investigator, may adversely affect the safety and/or efficacy of the study drug or severely limit that patients life-span or ability to complete the study (eg, alcohol or drug abuse, disabling or terminal illness, mental disorders);Treatment with any of the following medications;
Oral corticosteroids within 3 months of screening. Treatment with systemic corticosteroids is also prohibited during study participation;Chronic stable use, or unstable use of NSAIDs (other than low dose aspirin) is prohibited. Chronic use is defined as >3 consecutive or non-consecutive days of treatment per week. In addition intermittent use of NSAIDs is strongly discouraged throughout the study and NSAIDs if required, must not be used for more than a total of 2 days. For those requiring analgesics during the study, paracetamol is recommended.The use of short-acting nitrates (eg, sublingual nitroglycerin) is permitted. However, participants should not take short acting oral nitrates within 4 h of screening or an subsequent visit;The use of long-acting nitrates (eg, Isordil) is permitted but the dose must be stable for at least 2 weeks prior to screening and randomisation;The use of sympathomimetic decongestants is permitted, however, not within 1 day prior to any study visit/BP assessment;The use of theophylline is permitted but the dose must be stable for at least 4 weeks prior to screening and throughout the study;The use of phosphodiesterase type V inhibitors is permitted; however study participants must refrain from taking these medications for at least 1 day prior to screening or any subsequent study visits;The use of α-blockers is not permitted, with the exception of afluzosin and tamsulosin for prostatic symptomsA pill count will be made at the end of the 4 week run-in period and those with adherence <70% will be excluded from randomisation

#### Recruitment and randomisation of participants

Potentially suitable patients are identified from hospital and general practice populations. Written informed consent is obtained from participants by a medical investigator. The research nurse records baseline variables, takes blood and urine for baseline biochemistry and haematology, and records the medical history. Blood samples are analysed at the local health service laboratory according to usual practice. Serum for future analyses and blood for future genetic analyses are stored by centres. Participants who have given informed consent and meet the inclusion and exclusion criteria at the end of a month's placebo run-in are randomised to receive one of the possible sequences of the four trial treatments, each in addition to any other antihypertensive drug being taken at the time of randomisation. This is performed by contacting a central computerised randomisation facility based at the Robertson Centre for Biostatistics, University of Glasgow, by telephone or via a web-based service.

### Study objectives and end-points

#### Primary objective

The primary study objective is to test the hypothesis that the commonest cause of resistant hypertension is excessive sodium retention, and that ‘further diuretic therapy’, that is, spironolactone will be superior to other potential ‘add-on drugs’ for people with resistant hypertension, that is, inadequate BP control despite treatment with maximal/best tolerated doses of the three drug classes A+C+D, as recommended by the current NICE treatment guidelines algorithm.

#### Secondary objectives

The main secondary objective is test the use of plasma renin measurement to evaluate the ‘α, β, Δ’ rule^8^ for the selection of the fourth-line drug for patients with drug resistant hypertension—where α represents α-blockade, β represents β-blockade and **Δ** represents ‘further diuretic therapy’. We propose that α-blockade will be the most effective fouth-line treatment at lowering BP in patients in the mid-tertile of plasma renin (expected to be ≥20 mU/L but <100 mU/L); β-blockade will be the most effective drug when the renin level in in the top tertile (expected to be ≥100 mU/L) as this drug inhibits renin secretion; further diuretic therapy with spironolactone will be the most effective drug in the lowest tertile of plasma renin (<20 mU/L), indicative of renin suppression due to excessive sodium retention. Further secondary analyses will use physiological phenotyping of non-invasive haemodynamic parameters indicative of sodium retention and volume status, that is, cardiac output, peripheral vascular resistance, bio-impedance, pulse wave analysis and pulse wave velocity to evaluate mechanisms for resistant hypertension and determine if these methods can help better stratify the best treatment for individual patients with resistant hypertension.

### Study procedures

#### Clinic blood pressure measurement

Seated clinic blood pressure will be measured at each clinic visit in accordance with the methods recommended by the British Hypertension Society,^13^ using an automated, approved and validated BP monitor (Microlife Watch BP, Microlife) with an appropriate cuff size applied to the non-dominant arm. Three measurements will be recorded 1 min apart, after 5 min rest and seated, and the average of the last 2 measurements will be recorded as the clinic BP.

#### Home blood pressure monitoring

The HBPM systolic BP average will be used for the main study end points. At several points during the trial, HBPM readings will be recorded (immediately prior to randomisation and at the end of 6 and 12 weeks of each treatment cycle). BP will be measured using the non-dominant arm, using the same BP monitor used for the clinic BP measurement which will be issued to the patient for use throughout the trial. BP readings will be taken in the morning and in the evening, ideally at the same times throughout the study, for example, ∼08:00 and 20:00—or the nearest time to these that is convenient for the patient. HBPM readings will be taken on four consecutive days prior to a study visit. Participants will be asked to make triplicate readings, 1 min apart, after 5 min seated rest, and to record these on the pro forma provided. All readings will also be captured automatically by the monitor. For analysis, a maximum of the last 18 recordings (ie, days 2–4, if all completed) will be used. If the patient fails to comply with the recommended number of recordings, a minimum of six BP recordings is required for a valid measurement of the HBPM average.

#### Plasma renin measurement

Plasma renin levels will be measured using a Diasorin Liaison automated chemiluminescent immunoassay for direct renin*.* Performed in Cambridge (English centres) and Edinburgh (Scottish centres).

#### Assessment of drug treatment compliance

It is recognised that poor concordance with drug treatment contributes to apparent drug treatment resistance. Robust checks for treatment concordance are included in the study procedures: (1) At baseline and as a prerequisite for randomisation, patients will be witnessed consuming their usual BP medications (A+C+D) in the clinic and then HBPM will be performed over the next 6 h to confirm that their BP is not controlled with their usual treatment; (2) Tablet counts will be performed at baseline (end of placebo run-in) and after 12 weeks of each treatment cycle, and patients with less than 70% tablet consumption will be deemed non-concordant with their medication; (3) Serum ACE levels will be measured to provide a retrospective measure of treatment concordance; (4) Urine samples will be stored frozen at −20°C at selected sites throughout the study, for analysis of urinary drug metabolites at a single site (University of Leicester) using high-performance liquid chromatography/mass spectroscopy to provide a retrospective analysis of treatment concordance with individual drugs.^14^

#### Non-invasive phenotypic profiling of haemodynamics and volume status

Non-invasive haemodynamic measures (cardiac output, peripheral resistance, bioimpedance) using thoracic bioimpedance cardiography (Cardiodynamics USA) and pulse wave analysis and pulse wave velocity measurements (Sphymocor, Australia, or equivalent) will be recorded at baseline and at the end of each treatment cycle at selected study sites.

#### Pharmacogenetics

Blood samples will be taken at baseline and the DNA extracted and stored for pharmacogenetic analysis. At the end of the study, these samples will be transferred from each site to Cambridge.

#### Safety assessments

All observed or volunteered adverse events considered related to treatment will be recorded on the adverse events section of the eCRF. Study staff will pursue and obtain information to confirm whether the event meets the criteria for classification as a serious adverse event. An event will be deemed serious if it results in death, is life-threatening, requires hospitalisation, results in persistent or significant disability/incapacity, is a congenital anomaly or birth defect, or is another medically important event. Adverse events will be classified according to seriousness, severity (mild, moderate or severe), causal relationship (certain, probably, possible, unlikely, unrelated) and expectedness. Suspected unexpected serious adverse drug reactions (SUSAR's) are not considered likely in this trial as there have been many years of experience with each of the trial drugs. All potential SUSAR's are subject to expedited reporting. Evaluations of blood pressure, blood counts, blood chemistry, urinalysis, ECGs, physical examination and monitoring of vital signs are scheduled to be performed at regular intervals and can be increased in frequency if required, at the discretion of the PI.

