**Trial registration number:**

Clinicaltrials.gov NCT02369081, EUDract number: 2008-007149-30.

Strengths and limitations of this study
Randomised, masked, adequately powered study of rigorously defined resistant hypertension;Rigorously characterised population of patients with resistant hypertension.Use of home blood pressure monitoring to evaluate the blood pressure response to treatment.The trial is not powered to detect the impact of drug treatment on morbidity and mortality.Spironolactone is not licensed for the treatment of hypertension in UK.

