#### Statistical model

The protocol requires patients to take triplicate morning and evening HBPM BP readings for the 4 days before each study visit, a total of 24 readings per visit. We shall use the arithmetic mean of last 18 measurements prior to a study visit to calculate home blood pressure. If more than 18 measurements have been obtained, the earliest recorded readings will be discarded. Thus, for most patients we will use all the readings on days 1 to 3 prior to the visit, but if any of these are missing then readings from day 4 will be used instead. The minimum number of measurements required for a valid assessment of home blood pressure using home BPM is six. Means of the morning and evening readings will be used in all subsequent analysis.

We shall use a mixed model to analyse HBPM BP, with unstructured covariances for the repeated measures for a patient. The model will include terms for time of day (morning or evening), gender, age, height, weight and smoking history. We will also adjust for baseline BP. If any of the baseline BPs cannot be estimated, we will substitute the overall mean baseline value, set an indicator variable to denote an imputed value and include the indicator variable in the model. The model will also include terms for treatment and phase (to allow for period effects), and an indicator variable to identify the subgroup of patients whose crossover treatments were unblinded.

*The primary analysis* will use BPs recorded for the maximum tolerated dose of each drug. The first of the primary end points is the mean difference between spironolactone and placebo; the second is the mean difference between spironolactone and the average of other active treatments; and the third and fourth are the mean differences between spironolactone and each of the other active treatments taken individually.

*The secondary analysis* will estimate for each treatment: changes in home BP; clinic BP on maximum tolerated dose, and changes in clinic BP; responder rates; withdrawals due to adverse events; and haemodynamic variables and pulse wave analyses. We shall use mixed models to analyse the continuous variables and these will include baseline covariates.

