#### Blinded versus unblinded cohorts

We will assess the advantage and disadvantages of using the double-blind, placebo-controlled random crossover design in comparison to the open label random crossover design. We will expand the models used to analyse the primary and secondary outcomes to estimate a cohort effect (unblinded vs blinded) within each treatment.

Patients who withdraw from the study before final visit will be included in the primary analysis if they have at least one postrandomisation HBPM, and missing data imputed by application of the last observation carried forward. Patients with data missing from any time point required for analysis, and patients in whom major violation of the protocol is documented by investigators or detected by the data management centre will be excluded from per-protocol analysis.

There will be no interim analysis, no stopping rules and no data monitoring committee. This is because all treatments are being used for licensed indications, and have been so used for several decades. We do not, therefore, anticipate any unexpected hazard that has eluded detection during many millions of person-years exposure, and the study is not powered to detect any significant differences in serious morbidity or mortality between treatment groups.

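### The article contradicts itself on whether an adverse event must be judged treatment-related before it is recorded, and its licensing ground for having no monitoring committee is contradicted for spironolactone

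*Protocol article*

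**What the plan says.** On recording, the article makes three statements that do not fit together.

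- Safety assessments, first sentence: "All observed or volunteered adverse events considered related to treatment will be recorded on the adverse events section of the eCRF".
- Later in the same paragraph, events are classified by "causal relationship (certain, probably, possible, unlikely, unrelated) and expectedness".
- Tolerability: "Adverse events are recorded in the electronic case record form at each visit". No relatedness condition is attached. Table 1 likewise schedules adverse-event reporting at every visit from week 6 to week 48.

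For analysis, the harm-related outcome named for comparison between treatments is in the secondary analysis under Statistical model: "responder rates; withdrawals due to adverse events; and haemodynamic variables and pulse wave analyses".

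On monitoring, the last paragraph of Blinded versus unblinded cohorts says "There will be no interim analysis, no stopping rules and no data monitoring committee", and gives as its first reason: "This is because all treatments are being used for licensed indications, and have been so used for several decades". It adds that no unexpected hazard is anticipated after very large past exposure, and that the study lacks power for differences in serious morbidity or mortality. The Strengths and limitations list near the front of the article says: "Spironolactone is not licensed for the treatment of hypertension in UK".

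**The concern.** Whether an event is related to treatment is an opinion, not an observation. If that opinion decides entry into the database, counts by treatment mix two things: how often events happened, and how readily the investigator blamed the treatment. An event in a period known to be placebo is less likely to be called treatment-related than the same event on an active drug. A filtered record can therefore show a drug-placebo difference where there is none, or distort a real one. An event that was never entered cannot be recovered from the case report form.

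The contradiction also matters in itself. A site working from the Safety assessments sentence and a site working from the Tolerability sentence would produce different datasets under one protocol. Pooled counts would then have no single definition.

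The licensing statement is a separate and smaller matter. It is offered as a reason for a monitoring decision, and the article contradicts it for the drug that appears in every primary comparison.

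**Working it through.** **1. The recording rule.** Take the two possible rules in turn.

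- Rule A (only related events entered): the Safety assessments first sentence fits. The two lowest grades of the causality scale would then have almost nothing to hold, and the Tolerability sentence would be wrong as written.
- Rule B (all events entered, causality graded afterwards): the causality scale, the Tolerability sentence and the Table 1 schedule all fit. The relatedness condition in the Safety assessments sentence would then be wrong.

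Neither rule fits all the statements. More of the text supports rule B, but the sentence that states what goes into the adverse-event section of the eCRF supports rule A.

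**2. What rule A would do to a comparison.** Let p be the true event rate in a treatment period and r the share of those events judged related. The recorded rate is p × r. The recorded drug-minus-placebo difference is

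p(drug) × r(drug) − p(placebo) × r(placebo).

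If the true rates are equal at p, this becomes p × [r(drug) − r(placebo)], which is zero only when the two shares are equal. The article gives neither p nor r for any treatment, so the size of the bias cannot be derived from it.

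**3. Where the judgement is made with treatment known.** Study design says the last 100 patients are studied open-label. The recruitment target reproduces: 294 / (1 − 0.15) = 345.9, rounded up to 346. The open-label share is 100 / 346 = 28.9%. The other 246 patients (71.1%) are in the blinded phase, where investigators and patients do not know the assignment. The 29% is the share of patients in whom the judgement is made unblinded. It is not a measure of bias.

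**4. Which named analysis is touched.** Withdrawals due to adverse events are to be estimated for each treatment, and withdrawal rates analysed by logistic regression. The article does not say that this outcome depends on the relatedness condition. What is exposed is any tabulation of adverse events by treatment, and the blinded-versus-open comparison if it is extended to adverse events.

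**5. The licensing statement.** The monitoring paragraph speaks of all treatments. The limitations list says spironolactone has no UK licence for hypertension, and Study participants places all 14 sites in the UK. Both statements cannot hold. The other two grounds, long use and lack of power for serious outcomes, do not depend on the licence and are unaffected.

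**The case against.** The strongest reply is that the first sentence of Safety assessments is loose wording. A scale running down to unrelated has no use unless unrelated events are entered, two other places record events without a filter, and this is a condensed article whose full protocol (version 9) is not shown. This stands to the extent that a filter cannot be called a settled design choice. It does not remove the contradiction, because the article states the rule and states it in two incompatible ways.

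A reader might infer that this record is the main protection for patients. The article does not support that. Table 1 schedules electrolytes, urea and creatinine at every visit whatever anyone thinks about causality. Serious events are followed up, suspected unexpected serious reactions go to expedited reporting, and a 24-hour unblinding service existed in the blinded phase.

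A reader might also infer that oversight rests solely on a false premise. It does not. Two other grounds are given, and an executive committee meeting at least quarterly is charged with responding to safety problems. That committee is not described as independent, but correcting the licence statement would not by itself overturn the decision. Whether to add a committee or by-treatment safety tables is a trade-off that this point does not decide.

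Finally, the trial is described as fully recruited, so a new entry rule can help only patients still being followed. That is true, and it shifts part of the remedy to reporting.

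**Conclusion.** Two internal contradictions are established from the text alone. The first is whether relatedness is a condition for recording an adverse event. If the Safety assessments sentence was applied as written, adverse-event counts by treatment are filtered by investigator judgement, made with treatment known in 100 of 346 patients (29%, taking the recruitment target as the denominator). Drug-versus-placebo comparisons of those counts could then be biased. This rests on two assumptions the article cannot confirm: that sites followed that sentence, and that events are called related at different rates on drug and on placebo. The size is not computable, and any percentage put on it would be invented. It would go too far to say that the harms comparison is known to be filtered.

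The second is that one of the stated grounds for having no data monitoring committee is contradicted for spironolactone. That calls for correction of the rationale and does not show that a committee was required.

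Neither contradiction affects the primary blood pressure comparisons. Both should be corrected, because the first bears on the credibility of any harm comparison and the correction is cheap.

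**What to change.** - In Safety assessments, delete the relatedness condition from the first sentence, so that it agrees with Tolerability and with the causality scale. All adverse events are then recorded, with causality as an attribute of each. Compare all-cause events by treatment, with any related-only tabulation as a supplement.
- Because recruitment is complete, state in the report which rule sites actually applied. If it was the filtered one, or if sites differed, say so and limit the harm claims accordingly.
- In the monitoring paragraph, correct the statement on licensed indications so that it agrees with the limitations list, and give the reasons for having no committee on the remaining grounds of long use and lack of power for serious outcomes.

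The cost is a change of wording, eCRF guidance to sites still following patients, slightly more adverse-event entry, and one check with sites on past practice. Events already left out under a filtered rule cannot be restored by a change of wording.
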